**4-5.** **Overview of Research Chemicals and Equipment**

As stated in 2-2. Information on medical devices used in the clinical trial

**4-6 Research Procedures**

**4-6-1 Research implementation system**

This clinical trial will be conducted as part of the "Obtaining Evidence of Efficacy of LED Optical Acupuncture and Moxibustion" project (project leader: [name], Graduate University of the Creation of New Photonics Industries), which was adopted as an industry-academia-government-finance collaboration innovation promotion project, and for which Sasiperere Japan Ltd. applied. The LED acupuncture and moxibustion device to be evaluated is an unapproved medical device, and the clinical trial to be conducted to evaluate its safety and efficacy falls under the category of specified clinical trial and must therefore be conducted at a medical institution. Therefore, the University decided to participate in the project. Neither the principal investigator ([name]) nor the sub-investigator ([name]) has acupuncture and moxibustion skills or national certification, so the treatment will be performed by Zenba Acupuncture and Moxibustion Clinic's [name] (acupuncturist) under the supervision of Drs. (former professor at St. Christopher's University, now Health Data House Corporation (Iwate University venture)) and [name] of the Graduate University for the Creation of New Photonics Industries will be in charge of echo, electromyography, and thermography, while [name] of the University will be in charge of baroreceptor reflex sensitivity and autonomic nerve function.

**4-6-2　Protocol Treatment**

　Study Design

Single-arm, open-label, uncontrolled, single-comparison study

Treatment with research equipment

Efficacy and safety assessment

Obtaining written consent

Eligibility Verification and Registration

<Protocol Treatment>

The position of the patient during the protocol is the sitting position, and the following order is used.

[At the time of obtaining consent]

After obtaining consent, a questionnaire (background investigation) will be conducted.

[Before treatment]

1. After resting for 5 minutes, vital signs will be measured.
2. The research subject will fill out the questionnaire (before the procedure).
3. Observe the skin at the treatment site.
4. Measurements will be made in the following order: muscle ultrasonography of both shoulders, surface electromyography, thermography, and pressure pain threshold. At the end of the electromyography, continuous blood pressure monitoring and continuous measurement of heart rate variability are performed.
5. The results of the examination are confirmed, and the treating side is decided.

(Criteria for determining the treating side)

The side with the lower pressure sore meter reading is the treatment side.

[Treatment] 1.

1. irradiate LED light acupuncture needles to the shoulder well (a common acupuncture point for stiff shoulders).

（Irradiate the silicon rubber part of the LED acupuncture needle directly onto the skin of the shoulder well for 30 seconds per irradiation. After irradiation, check the condition of the skin, and continue irradiation after 3 seconds until the skin shows a reddish change to the naked eye from before irradiation. Repeat irradiation up to 6 times.

[Immediately after the treatment]

1. Immediately after the LED acupuncture irradiation, skin observation, thermography, and pressure pain threshold (on the treated side only) should be performed. (After the measurement, cover the treated area with a bath towel.
2. The research subject will fill out the questionnaire (immediately after the treatment).

[15 minutes after the treatment].

1. 15 minutes after the end of irradiation, skin observation, thermography, pressure pain threshold (on the treated side only), muscle ultrasonography, and surface electromyography are measured in this order. The Finapres NOVA will be removed when the tenderness meter measurement is completed.
2. The research subject will fill out a questionnaire (15 minutes after the treatment).
3. After 5 minutes of rest, vital signs will be measured.

[Post-procedure observation: 7 ± 2 days after the procedure.

Skin observation will be performed to evaluate safety.

<Examination and evaluation methods

1. Vital signs: Blood pressure and pulse are measured using a sphygmomanometer.
2. Tension and tenderness meter: Measure the circumference of the shoulder well within 10 mm in diameter twice, and calculate the average value.
3. Thermography:
   1. Measure the body surface temperature of the subject's entire body.
   2. Measure body surface temperature within a range of about 10 cm centered on the area irradiated with LEDs.
4. Continuous blood pressure, heart rate, heart rate variability, and BRS test: Measurements will be made using electrocardiogram electrodes and Finapres NOVA.
5. Surface electromyography: Weight-loading test is performed on the shoulder of the treatment site, and muscle fatigue caused by the loading is evaluated by surface electromyography.
   1. Perform the test in a sitting posture. (2) The subject's arms are placed on a desk at rest, and after a 15-second measurement at rest, a 2-minute measurement of (weight) loading is performed.
   2. The load is applied by holding a 2- to 3-kg weight on the treating side and holding it as follows The upper arm is held horizontally forward and the forearm is flexed 90 degrees vertically upward for 15 seconds, and then the forearm is held in extension for up to 2 minutes with the weight and measured. The arm of the non-treated side should be in a posture to support the upper body so that the muscle load on the trunk is excluded. The loading time is 2 minutes, but may be shortened if the subject does not tolerate the weight load or the maintenance of the posture. (When shortening the loading time, the change in EMG from the state of no muscle fatigue to the state of fatigue is measured, so there will be few problems in data collection.)
6. Measurement of the EMG load is performed on the shoulder on the side to be treated.

The measurement site should be the trapezius muscle (especially from the neck to the shoulder) and the deltoid muscle.

1. Muscle ultrasonography: Measurement is made simultaneously with the above surface EMG examination process.
   1. Echocardiography is performed on the trapezius muscles (especially from the neck to the shoulders) and deltoid muscles at rest and during loading.
   2. Avoid electrode positions for the above muscles when performing echo.
   3. A comparison of echo intensity (luminance, muscle contraction, muscle thickness, etc.) of the muscles under weight lifting is performed.

<Observational Examination/Item>.

After obtaining consent, the background of the research subjects will be investigated.

- Study subject background: age, gender, medical history of cervical spine disease, a survey of medications used
- Vital signs: blood pressure, pulse (heart rate), heart rate variability (LF, HF, LF/HF), baroreflex sensitivity (BRS)
- Clinical findings: skin observation (presence of redness)
- Thermography: skin surface temperature of the whole body and the area to be treated
- Pressure pain threshold: measurement of the circumference of the shoulder well within 10 mm in diameter
- Surface electromyography: measurement of the amplitude and frequency of surface electromyograms generated from the trapezius (especially from the neck to the shoulder) and deltoid muscles over time to determine muscle fatigue associated with loading.
- Muscle ultrasonography: measurement of muscle echo changes (e.g., brightness) over time in the trapezius (especially from the neck to the shoulder) and deltoid muscles during loading.
- Questionnaire: (Background survey) Daily living situation, (Before treatment)
- (Before the treatment) Pain due to stiffness in the shoulders (VAS), evaluation of stiffness in the shoulders (VAS)
- (Immediately after the treatment) Pain due to stiff shoulders (VAS), evaluation of stiffness in the shoulders (VAS), evaluation of sensation during the treatment
- (15 minutes after treatment) Pain due to stiff shoulders (VAS), evaluation of stiffness in the shoulders (VAS), evaluation of sensation during treatment (VAS)
- Adverse event (skin burn)

＜Schedule＞

|  | **VISIT 1** | **VISIT 2** | | | | **VISIT　3** |
| --- | --- | --- | --- | --- | --- | --- |
|  |  | **Day of treatment** | | | | **7 ±2 days after treatment** |
|  |  | Before the treatment | **Treatment** | Immediately after the treatment | 15 minutes after treatment |  |
| Obtaining written consent | **○^＊1^** | |  |  |  |  |
| Background evaluation | **○^*1^** | |  |  |  |  |
| Treatment |  |  | **○** |  |  |  |
| Vital Signs Assessment |  | **○** |  |  | **○** |  |
| Continuous blood pressure heart rate measurement, heart rate variability, BRS test ^*２^ |  |  |  |  |  |  |
| pressure pain threshold |  | **○** |  | **○** | **○** |  |
| Thermography |  | **○** |  | **○** | **○** |  |
| Muscle ultrasonography |  | **○** |  |  | **○** |  |
| Surface electromyography |  | **○** |  |  | **○** |  |
| Skin Observation |  | **○** | **○** | **○** | **○** | **○^*3^** |
| Adverse effect |  |  | **○** | **○** | **○** | **○^*3^** |
| Questionnaire |  | **○** |  | **○** | **○** |  |

*1 Perform either VISIT1 or VISIT2.

*2 If continuous blood pressure/heart rate measurement and BRS test cannot be performed, they will not be performed.

*3 Confirmation by telephone or e-mail is acceptable, but if the principal investigator deems it necessary, the patient must come to the hospital for confirmation.

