**9-1-3** **Analysis of secondary endpoints**

- On the treated side, the pre-, immediate post-, and 15-minute post-treatment tenderness meter and skin temperature measurements over time will be analyzed using one-way repeated measure ANOVA or Friedman's test.
- ~~One-way repeated measure ANOVA or Friedman's test will be used to analyze the pressure pain threshold, skin temperature, and subjective symptoms (VAS) measurements over time before, immediately after, and 15 minutes after the treatment on the non-treatment side.~~
- ~~Differences between the treated and non-treated sides of the pressure pain threshold, skin temperature readings, and subjective symptoms (VAS) over time before, immediately after, and 15 minutes after the treatment will be analyzed using two-way repeated measure ANOVA or Friedman's test.~~
- Heart rate variability frequency analysis will be performed to compare changes in the low frequency (LF) range and the power ratio of the low-frequency range to the high-frequency range (LF/HF) from before to 15 minutes after treatment. Average values will be taken before (5 minutes), ~~during (up to 3 minutes)~~, immediately after (5 minutes), and 15 minutes after (5 minutes) the procedure and analyzed using One-way repeated measures ANOVA or Friedman's test.
- Comparison of baroreceptor reflex sensitivity before, immediately after, and 15 minutes after the procedure

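### The autonomic baseline is recorded only after the EMG weight hold with no stated rest, while the post-treatment recording ends before the hold is repeated, so recovery from exertion can be read as a device effect

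*Protocol*

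**What the plan says.** **Before treatment (protocol 4-6-2).** The session opens with "After resting for 5 minutes, vital signs will be measured", followed by the questionnaire and skin observation. Then: "Measurements will be made in the following order: muscle ultrasonography of both shoulders, surface electromyography, thermography, and pressure pain threshold". The continuous recording is placed within that sequence: "At the end of the electromyography, continuous blood pressure monitoring and continuous measurement of heart rate variability are performed". The treatment side is chosen next, and irradiation follows.

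**The EMG test (4-6-2, examination methods).** "The load is applied by holding a 2- to 3-kg weight on the treating side", first with the forearm flexed for 15 seconds and then with it extended. "The loading time is 2 minutes, but may be shortened if the subject does not tolerate the weight load or the maintenance of the posture".

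**At 15 minutes (4-6-2).** Skin observation, thermography and pressure pain threshold come first, then ultrasonography and EMG. "The Finapres NOVA will be removed when the tenderness meter measurement is completed". The recorder is therefore off before the second hold.

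**Analysis (9-1-3).** For HRV, "Average values will be taken before (5 minutes"), then "immediately after (5 minutes), and 15 minutes after (5 minutes) the procedure", with repeated-measures ANOVA or Friedman's test on LF and LF/HF. BRS is compared at the same three times, with no window length given. The design is single-arm and uncontrolled (4-6-2).

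**The concern.** A before-and-after comparison without a control arm relies on the two measurements being taken under like conditions. Here they differ, in every subject and in the same direction, in the time since a fatiguing hold. Any autonomic response to the hold that has not faded by the baseline window will appear as a change after treatment.

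The background (2-1) expects near-infrared light to act partly through sympathetic inhibition. If the hold leaves sympathetic tone raised for a time, which is an assumption because the documents are silent on it, recovery would move the indices in the direction that the hypothesis predicts. Autonomic function and BRS are named in the study purpose (section 3), so the conclusion about mechanism is what is at stake.

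There is a smaller, separate point. The last 5-minute average is planned without any rule that keeps the recorder on for 5 minutes after the 15-minute mark.

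**Working it through.** **1. Order of events (4-6-2).**

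| Step | Before treatment | 15 minutes after |
|---|---|---|
| 1 | 5-minute rest, vital signs, questionnaire | Skin observation |
| 2 | Skin observation, ultrasonography | Thermography |
| 3 | EMG with weight hold | Pressure pain threshold |
| 4 | **Recording starts** | **Recorder removed** |
| 5 | Thermography, pressure pain threshold, choice of side | Ultrasonography |
| 6 | Irradiation | EMG with weight hold |

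The first hold precedes the whole recording and the second follows it. All baseline data are post-exertion. The post-treatment data are separated from the only earlier hold by the remaining baseline tests, the irradiation and, for the last window, the waiting time. Irradiation lasts at most 6 × 30 s + 5 × 3 s = 195 s.

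**2. Is the last window complete?** Section 9-1-3 does not say where the 5 minutes lie.
- Minutes 10 to 15: complete before the 15-minute measurements start.
- Minutes 15 to 20: complete only if skin observation, thermography and pressure testing together last at least 5 minutes. The protocol gives no duration for them.

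**3. Illustrative size.** The sample of 10 has no statistical basis (9-3), so there is no planned figure to reproduce. The carry-over *d*, in within-subject SDs, is assumed.

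Inputs: n = 10 (4-2-1), three time points (9-1-3), significance level 0.05 (9-4), no device effect, baseline mean shifted by *d*, no shift in the later windows. For one-way repeated-measures ANOVA, F has 2 and 2(n−1) = 18 degrees of freedom and non-centrality

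λ = n × Σ(μⱼ − μ̄)² = n × (2/3) × d².

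| d | λ at n=10 | P(p<0.05), ANOVA | Friedman (simulated) |
|---|---|---|---|
| 0 | 0 | 5% | 4% |
| 0.25 | 10 × 0.667 × 0.0625 = 0.42 | 8% | 6% |
| 0.5 | 10 × 0.667 × 0.25 = 1.67 | 17% | 13% |
| 1.0 | 10 × 0.667 × 1 = 6.67 | 55% | 41% |

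The ANOVA column comes from 40,000 simulated trials per row; the non-central F distribution with these λ gives the same values to within 1 percentage point. The Friedman column comes from 8,000 simulated trials per row.

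Two variations:
- With 7 evaluable subjects, the upper end of the range in 9-3, the ANOVA rates for d = 0.25, 0.5 and 1.0 are 7%, 13% and 38%.
- If half the shift is still present in the immediately-after window, the n=10 rates at d = 0.5 and 1.0 are 14% and 44%.

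**The case against.** The strongest reply is that the protocol fixes when recording starts, not where the 5-minute baseline average lies. Thermography, pressure testing and the choice of side all come between the hold and irradiation. The last 5 minutes before irradiation could be used, and the response to the hold may have faded by then. Exact window limits are commonly left to a SAP. This stands in part: missing window limits alone would not be a finding, and a reader should not infer that the baseline window begins directly after the hold. But a SAP can only choose among data that were recorded. It cannot supply a pre-hold baseline, or a rest after the hold that the procedure did not include.

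Three further inferences go beyond the documents:
- **That recorder removal cuts the last window.** It does so only if the window is minutes 15 to 20 and the three measurements take under 5 minutes. Minutes 10 to 15 would be complete.
- **That pressure testing biases the baseline.** It is done at all three time points, so it is largely a shared condition. Only the hold is asymmetric.
- **That recovery will produce a false autonomic effect.** The documents do not say how far or for how long the hold alters LF/HF or BRS. It can produce one; no more is supported.

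It is also fair to say that these are secondary endpoints in a 10-person feasibility study, that the schedule footnote allows the measurements to be omitted, and that an uncontrolled design limits attribution anyway. That lowers the stakes. It does not excuse an avoidable systematic difference between before and after.

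**Conclusion.** The point holds in a limited form. The stated order makes every autonomic baseline a post-exertion record with no stated rest, and gives no post-treatment record a fresh hold before it. Without a control arm, recovery from the hold is confounded with any device effect on LF, LF/HF and BRS. Separately, a last window of minutes 15 to 20 has no guarantee of completeness.

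The size is unknown. False-positive rates of about 8% to 55% rest on an assumed shift of 0.25 to 1.0 within-subject SD at n=10, and fall to the nominal 5% if nothing carries over. The point is confined to secondary endpoints; the pre-treatment VAS is completed before the hold. It should be corrected because the remedy is simple and the loss cannot be fully repaired at analysis.

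**What to change.** 1. **Baseline (4-6-2).** Record the 5-minute autonomic baseline in seated rest before ultrasonography and EMG, for example joined to the existing 5-minute rest; or record it after a stated rest following the hold. The first option leaves the hold between baseline and irradiation, so any residue would fall in the immediately-after window. The second avoids this if the rest is long enough. The documents do not determine that length, so the investigators must choose and state it.
2. **Last window (4-6-2 and 9-1-3).** Place it in the period before the 15-minute measurements, for example minutes 10 to 15; or remove the recorder only when the full 5 minutes are complete.
3. **BRS (9-1-3).** Use the same three windows as for HRV.

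**Cost.** A few extra minutes of set-up or rest in a session that section 12-3 puts at about one hour, and a protocol amendment. With a pre-hold baseline, the recorder must either stay on through the hold or be refitted after it. No new equipment or additional subjects are needed.

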**4.** **Matters related to the content of the clinical trial**

**4-1.** **Primary and secondary endpoints**

**4-1-1.** **Primary endpoints**

Subjective symptoms (VAS)

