**4-3.** **Inclusion and exclusion criteria for study subjects**

**4-3-1.** **Inclusion criteria**

The following selection criteria will be applied to those who meet all of the following criteria

1. men and women 20 years of age or older

2. who are aware of shoulder stiffness

3. Persons who have given their consent to this study by signing a consent form.

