**4-3-2　Exclusion criteria**

Patients who meet at least one of the following exclusion criteria will be excluded.

1. those with diseases of the cervical spine (cervical spondylosis, herniated disc, intervertebral arthritis, cervical sprain, etc.)

2. those who are being treated by a physician for stiff shoulders

3. who habitually receive treatment for stiff shoulders or self-care (e.g., compresses, oral medication, acupuncture, moxibustion, massage)

4. who has skin abnormality from the neck to the back

5. who are deemed inappropriate by the Principal Investigator (or Co-Principal Investigator).

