**9-1-2 Analysis of the primary endpoint**

Subjective symptoms (VAS) measured over time before, immediately after, and 15 minutes after the procedure at the treatment site will be analyzed using one-way repeated measure ANOVA or Friedman's test.

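### The entry criterion, the side rule and the treatment-site VAS are not tied together, so a subject stiff on one side can be treated on the symptom-free shoulder and still count in the primary analysis

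*Protocol*

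**What the plan says.** - **Primary endpoint (section 4-1-1):** "Subjective symptoms (VAS").
- **Primary analysis (section 9-1-2):** "Subjective symptoms (VAS) measured over time before, immediately after, and 15 minutes after the procedure at the treatment site will be analyzed" by one-way repeated measures ANOVA or Friedman's test.
- **Entry (section 4-3-1):** besides age and consent, the only symptom criterion is being a person "who are aware of shoulder stiffness". Side, severity and a minimum score are not mentioned.
- **Exclusions (section 4-3-2):** "those who are being treated by a physician for stiff shoulders", people "who habitually receive treatment for stiff shoulders or self-care", and those "who are deemed inappropriate by the Principal Investigator". The last names neither a side nor a score.
- **VAS items (section 4-6-2):** "Pain due to stiffness in the shoulders (VAS), evaluation of stiffness in the shoulders (VAS"), with no side given.
- **Choice of shoulder (section 4-6-2):** "The side with the lower pressure sore meter reading is the treatment side". The questionnaire is step 2 before treatment. The side is decided at step 5 and does not draw on the questionnaire.
- **Sample (section 9-3):** 10 subjects, from a feasible minimum of about 5-7 plus an allowance for dropouts, with no statistical basis.

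**The concern.** The primary endpoint is a felt symptom at one place, but the place is picked by a different instrument. Take a person stiff on the right only whose left shoulder gives a marginally lower pressure reading. Following the protocol, the site treats the left. If the VAS is then read for the treated shoulder, it starts near zero and has no room to fall. If it is read for the shoulders in general, it mainly describes a shoulder that was not irradiated. Either way, the subject says little about whether the device relieves stiffness where it was applied.

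With so few subjects, one or two such people pull the mean change towards zero and cost power. On the items the protocol lists, they also could not be identified afterwards.

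**Working it through.** **1. Does another provision catch it?** The exclusion table in section 9-6 has four rows: no treatment received, no efficacy assessment, breach of the selection criteria, and deviation from the protocol. A subject treated on a symptom-free shoulder was treated, was assessed, met the entry criteria and followed the side rule. None of the four rows applies, so the subject stays in the FAS and the PPS, and the PPS sensitivity analysis cannot show the problem. The background items in section 4-6-2 are age, gender, cervical spine history, medications and daily living situation; the stiff side is not among them.

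**2. Loss per affected subject.** Assume such a subject contributes zero change. The share of the mean effect lost is 1/n:
- n = 10: 1/10 = 10%
- n = 7: 1/7 = 14%
- n = 5: 1/5 = 20%

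**3. How often?** The protocol gives no input for this, so the following rests on assumptions. Let d be the amount by which the stiff side reads lower on average, in SDs of the side-to-side difference. Among people stiff on one side only, the rule picks the other shoulder with probability Φ(−d). Let s be the share of such people, taken as 10% to 30%. The expected number among 10 subjects is 10 × s × Φ(−d).

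| d | Φ(−d) | s = 10% | s = 30% |
| --- | --- | --- | --- |
| 0 | 0.50 | 0.5 | 1.5 |
| 0.5 | 0.31 | 0.3 | 0.9 |
| 1 | 0.16 | 0.2 | 0.5 |

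The expected dilution of the mean is s × Φ(−d), which runs from 0.10 × 0.16 = 1.6% to 0.30 × 0.50 = 15%. The d = 0 row supposes that tenderness says nothing about stiffness, so it is the pessimistic end.

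**4. Effect on power, for illustration.** The protocol states no effect size or SD to reproduce. Assumptions: 0-100 VAS, baseline mean 50 and SD 15, a fall of 15 mm at both later times, SD of change 15 mm, and affected subjects near zero throughout. Each scenario had 2,000 simulated trials at the 0.05 level.

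| n | Affected | ANOVA power | Friedman power | Mean fall (mm) |
| --- | --- | --- | --- | --- |
| 10 | 0 | 86% | 69% | 14.7 |
| 10 | 1 | 81% | 56% | 13.3 |
| 10 | 2 | 73% | 45% | 11.7 |
| 7 | 0 | 67% | 52% | 14.8 |
| 7 | 1 | 56% | 37% | 12.8 |
| 7 | 2 | 41% | 23% | 10.6 |

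**The case against.** The strongest reply is that the side rule is sensible. A lower pressure pain threshold marks the more tender shoulder, which will often be the stiffer one, and a fixed measured rule limits operator choice in an open-label study. Section 2-1 also describes stiffness as a complaint of the whole neck and shoulder region, so many subjects may be stiff on both sides. This stands, and it is why treatment of a wholly symptom-free shoulder is probably uncommon.

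The study is also called a feasibility study, and its sample size was not set statistically. A null result from 10 uncontrolled subjects would be inconclusive anyway. This stands too and limits the weight of the point, although section 9-4 still applies a significance level to the primary test.

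The questionnaire form itself is not shown and may already ask for the side. If so, only the protocol text needs correcting.

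A reader might go further and infer that a floor effect is to be expected, because there is no minimum VAS and exclusions 2 and 3 remove people under treatment or habitual self-care. The documents do not establish that. The milder-case effect is an inference, since those exclusions also remove people whose symptoms are masked by care. Criterion 2 requires awareness of stiffness, and sections 4-7-1 and 4-8-1 bar treatment and self-care for the 3 days before the procedure. A near-zero score at entry is possible but not shown to be typical.

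**Conclusion.** The gap is real: four parts of the protocol that must agree do not refer to one another, and no other provision catches the resulting case. The size per affected subject is firm arithmetic given zero contribution: about 10% of the mean effect at n = 10, and 14-20% at n = 7 to 5. The frequency is not known. Under the assumed ranges it is roughly 0.2 to 1.5 subjects in 10, probably towards the lower end.

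Two stronger readings are not supported. The 50%, 31% and 16% figures apply only to people stiff on one side, so they are not the proportion of all subjects treated on the wrong shoulder. Nor does the gap suggest a spurious benefit, because its direction is dilution. It is worth correcting because the correction is cheap and cannot be made after treatment, not because it invalidates the study.

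**What to change.** 1. Reconcile the entry criterion (4-3-1), the side rule (4-6-2) and the treatment-site VAS (9-1-2), so that the treated shoulder is one with the symptom being scored. How to do this is a clinical decision for the sponsor; no side rule is proposed here.
2. Record the stiff side or sides on the background questionnaire, before the treated side is decided.
3. Score the primary VAS for the treated shoulder. Because the pre-treatment questionnaire is completed before the side is chosen, the pain and stiffness items need to be asked for left and right at that time.
4. Add a sensitivity analysis of the primary endpoint without subjects whose treated side was not reported as stiff.
5. Report the distribution of the baseline VAS, so that a floor effect can be seen if there is one.

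A minimum VAS for entry is not recommended. In a single-arm before-and-after study, selecting on a high score invites regression to the mean in the device's favour. A separate screening score would protect little, because the schedule footnote lets consent and background evaluation fall on the treatment day.

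**Cost:** a protocol amendment, a few extra questionnaire lines, and one more analysis on a very small sample, to be read descriptively.

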**4-1-2. Secondary endpoints**

Skin temperature, pressure pain threshold, heart rate variability, baroreceptor reflex sensitivity, adverse events

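### The pressure reading that selects the treated side is also the baseline of the pressure-pain test, so this secondary endpoint is expected to be biased towards a rise

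*Protocol*

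**What the plan says.** In 4-6-2, pressure pain threshold is the last of the listed measurements before treatment. Then "The results of the examination are confirmed, and the treating side is decided", under the criterion "The side with the lower pressure sore meter reading is the treatment side". I read the pressure sore meter as the tenderness meter named elsewhere, a translation variant. Each value is the mean of two readings: "Measure the circumference of the shoulder well within 10 mm in diameter twice, and calculate the average value".

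The schedule has one pre-treatment entry for pressure pain threshold, and the text goes from the choice of side straight to irradiation. Immediately after treatment, "skin observation, thermography, and pressure pain threshold (on the treated side only) should be performed". The 15-minute reading is likewise limited to that side.

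Section 9-1-3 states the analysis: "On the treated side, the pre-, immediate post-, and 15-minute post-treatment tenderness meter and skin temperature measurements over time will be analyzed", by one-way repeated-measures ANOVA or Friedman's test. Section 9-4 applies p<0.05 to every test. The design is a "Single-arm, open-label, uncontrolled, single-comparison study". Pressure pain threshold is a secondary endpoint in 4-1-2: "Skin temperature, pressure pain threshold, heart rate variability, baroreceptor reflex sensitivity, adverse events". The primary endpoint is VAS.

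**The concern.** The value that decides which shoulder is treated then becomes the starting point of the comparison. A shoulder can be the lower one because it is truly more tender or because its reading happened to fall low. The second component does not persist, so later readings on that shoulder are expected to be higher with no treatment effect. The later readings are not selected, so nothing offsets this.

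A rise in threshold is the direction that would be read as benefit. Change in pain threshold is part of the research question (2-0) and of the purpose (section 3). A significant result in 9-1-3 could therefore be reported as a device effect when part or all of it comes from how the side was chosen. A larger sample would not help: the bias stays the same and the test becomes more likely to detect it.

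**Working it through.** **Plan's own figure.** There is none to reproduce. Section 9-3 says the number of cases has no statistical basis: about 5-7 evaluable subjects at minimum, with 10 enrolled.

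**Inputs from the protocol.** Two readings averaged per time point (4-6-2); the lower side selected (4-6-2); three time points on that side, ANOVA or Friedman (9-1-3); 5% level (9-4); 10 subjects, possibly 5-7 evaluable (9-3).

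**Assumptions, not in the protocol.** Independent normal reading errors with single-reading SD 1; true left-right difference with mean 0 and SD τ, in single-reading SDs; no treatment effect.

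**Bias.** The error of a two-reading mean has variance 1/2. The observed left-right difference has variance τ² + 1/2 + 1/2 = τ² + 1, and its covariance with the error of one side is 1/2. Conditioning on that side being the lower one:

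expected baseline error = −(1/2)/√(τ²+1) × √(2/π) = −0.399/√(τ²+1) single-reading SDs.

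Dividing by 0.707, the SD of a two-reading mean, gives 0.564/√(τ²+1): 0.56, 0.40, 0.25 and 0.18 SD for τ = 0, 1, 2 and 3. Later readings return upward by this amount.

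**False-positive rate of the nominal 5% test** (simulation under zero effect, 40,000 trials per setting):

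| Subjects | Test | τ=0 | τ=1 | τ=2 | τ=3 |
|---|---|---|---|---|---|
| 10 | ANOVA | 22% | 13% | 8% | 6% |
| 10 | Friedman | 17% | 10% | 6.5% | 6% |
| 7 | ANOVA | 15% | 10% | 7% | 6% |
| 7 | Friedman | 14% | 9% | 7% | 6% |

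At 5 subjects and τ = 0, 1, 2 the rates are about 12, 8 and 6% (ANOVA) and 9, 6 and 5% (Friedman).

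**Second parameterisation.** Set the between-person SD of the observed session mean to 1. Let s² be its error variance (1 − ICC) and t² the side-specific true variance (ICC × (1 − true left-right correlation)). The bias is s²/√(π(s²+t²)). With ICC 0.80 and correlation 0.90 (assumed), s² = 0.20 and t² = 0.08, so the bias is 0.20/√(π × 0.28) = 0.21 SD. Over ICC 0.60-0.95 and correlation 0.70-0.95 the bias runs from 0.05 to 0.34 SD, always upward. At 10 subjects the ANOVA rejects in 7.0-20.9% and Friedman in 5.9-16.0%.

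**With a fresh baseline on the chosen side.** Bias 0; at 10 subjects the ANOVA rejects in about 5% and Friedman in 4.4-4.8%.

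**Splitting the two existing readings** (select on the first, use the second as baseline). With independent errors the bias is 0, but the standard error of the change grows by √(1+0.5)/√(0.5+0.5) = 1.22. If half the error variance is shared by the two back-to-back readings (assumed), about 60% of the planned bias remains and the ANOVA rejects in 6-10% at 10 subjects for τ = 0 to 2.

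**The case against.** The strongest case against concerns weight rather than mechanism.

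- **Rank of the endpoint.** It is secondary, and 7-1 leaves it out of its list of secondary efficacy endpoints. This stands and lowers the severity, although 4-1-2 and 9-1-3 both keep the endpoint.
- **Uncontrolled feasibility study.** Even with a clean baseline, a pre-to-post change could not be attributed to the device. This also stands. The selection rule nevertheless adds a bias of known direction that is avoidable without a control group.
- **Size.** The 22% figure needs no true left-right difference in anyone, the ANOVA and all 10 subjects evaluable. This stands: it is a limiting case, and with a large true difference or few subjects the inflation is slight.
- **Sequence.** Electromyography precedes the pressure reading that fixes the side, yet its load is applied on the side to be treated. That needs reconciling, but the schedule still shows only one pre-treatment pressure reading.

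A reader might infer that the primary result is compromised too. The documents do not support that: VAS does not select the side, and the pre-treatment questionnaire is completed before the choice. A reader might also infer that the data could never reveal the problem. That is too strong. If the individual bilateral readings are kept, the bias can be roughly estimated as 0.399 × (single-reading error variance)/(SD of the observed left-right difference). This is a lower bound if the two readings share error, and imprecise with 10 subjects.

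Restoring the struck-out comparison with the untreated side would not help. That side is selected high and would be expected to drift down, widening the artefact.

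**Conclusion.** The point holds for pressure pain threshold. The direction of the expected bias follows from the protocol's own sequence, provided the readings carry some error; averaging two readings reduces that error without removing it. The amount cannot be fixed from the documents. Under the stated assumptions, false positives at 10 subjects run from about 6% to 22% with ANOVA and from about 6% to 17% with Friedman. At 7 subjects they run from about 6% to 15% and from about 6% to 14%. Choosing Friedman over ANOVA does not cure it. It is an expected upward bias of unknown size, not a demonstrated false rise. It should be fixed, but as a flaw in one secondary endpoint it does not undermine the primary analysis.

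**What to change.** Keep the rule for choosing the side. In 4-6-2, state that the bilateral pressure readings serve only that choice and that two new readings are then taken on the chosen side just before irradiation. In 9-1-3, define the pre-treatment pressure value as the mean of those two new readings. The cost is about a minute per subject and one sentence in each section.

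The new readings should be a separate measurement, with the instrument reapplied. Any error component that carries over from the selecting readings but has faded by the post-treatment readings would leave some bias.

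Selecting on the first existing reading and using the second as baseline needs no extra measurement, but it is only a partial remedy unless the two readings have independent errors. Whichever is chosen, record the individual readings for both sides so that the repeatability and the left-right spread can be reported.
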